## Abstract

People with multiple myeloma (MM) are second only to people with lung cancer for the poorest reported health-related quality of life (HRQoL) of all cancer types. Whether exercise can improve HRQoL in MM, where bone pain and lesions are common, requires investigation. This trial aims to evaluate the efficacy of an exercise intervention compared with control on HRQoL in people with MM. Following baseline testing, people with MM (*n* = 60) will be randomized to an exercise (EX) or waitlist control (WT) group. EX will complete 12-weeks of supervised (24 sessions) and unsupervised (12 sessions) individualized, modular multimodal exercise training. From weeks 12–52, EX continue unsupervised training thrice weekly, with one optional supervised group-based session weekly from weeks 12–24. The WT will be asked to maintain their current activity levels for the first 12-weeks, before completing the same protocol as EX for the following 52 weeks. Primary (patient-reported HRQoL) and secondary (bone health and pain, fatigue, cardiorespiratory fitness, muscle strength, body composition, disease response, and blood biomarkers) outcomes will be assessed at baseline, 12-, 24- and 52-weeks. Adverse events, attendance, and adherence will be recorded and cost-effectiveness analysis performed. The findings will inform whether exercise should be included as part of standard myeloma care to improve the health of this unique population.

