#### Stepped Down Supervision Approach

The modular multi-modal exercise program should be undertaken three times per week. For the first twelve weeks, two exercise sessions per week will be supervised by an AEP and once at home. For home-based sessions, elastic resistance bands will be provided, with advice for the purchase of dumbbells of appropriate weight. High intensity training will be replaced by a moderate intensity walk three times per week if a bike or treadmill is unavailable. Exercise supervision in the following three months will be stepped down to home-based sessions, with an optional weekly group class (2 to 6 participants) supervised by the study AEP. In addition, the AEP will telephone participants every two weeks to check on their adherence, any adverse events, prescribe progressions/regressions as appropriate, and answer any questions. Motivational interviewing will be used if any barriers are expressed. Following the first six months, all participants will be encouraged to maintain three exercise sessions per week for a further six months without group sessions. At the completion of their study involvement, participants will receive education regarding the Australian Government Department of Health Chronic Disease Management Plan, with no direct referrals to exercise physiologists or group classes.

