## 3. Outcome Measures

The data and sample collection schedule is depicted in Figure 1, and detailed in Table 1. All testing sessions will be conducted in the research laboratories within the School of Human Movement and Nutrition Sciences at The University of Queensland and will be completed by two researchers, consistently assigned to the same tasks. Prior to each testing session, participants will be asked to: (i) maintain a hydrated state in the 24 h prior to testing; (ii) fast, including abstaining from caffeine and alcohol intake for 8 h prior to testing; and (iii) avoid any vigorous, high or unaccustomed moderate intensity physical activity for the preceding 24 h. Wherever possible, the testing session will be scheduled for the morning hours, with all subsequent testing timepoints scheduled at the same time of day for each participant. Prior to the baseline testing session, participants will be required to record a 3-day diet diary, which they will be required to replicate prior to all subsequent testing sessions. Participant adherence to the testing standardization measures will be evaluated prior to the commencement of each assessment. If testing standardization measures are not met, the researcher will confirm the participant’s understanding of the pre-testing requirements and reschedule the assessment for another day. Inter- and intra-tester reliability will be determined for data-collecting investigators for all outcome measures as appropriate. Assessments will be performed in a consistent order with appropriate rest periods to minimize testing fatigue. Any alterations in medical status or medications, hospital admission, or concomitant study participation will be documented for future reference during analysis of results.

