#### 3.3.3. Adverse and Serious Adverse Events

Safety of the intervention will be measured through reporting adverse and serious adverse events. The trial AEP will record at each testing and supervised training session whether an adverse event has occurred and, if so, the AEP will provide details to the governing ethics committee. Events at unsupervised sessions will require self-report by the participant to the trial AEP. Adverse events will be reported to the study clinicians and the participant’s treating doctor for further decisions on safety and any required investigations. Trial insurance provided through the sponsor, The University of Queensland, includes provision for post-trial care if required.

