^a^ Baseline testing battery is repeated for waitlist control group after three months of usual care. ^b^ PACES-8 survey will be administered at 4-, 8-, and 12-weeks during the exercise intervention. ^c^ Adherence and safety will be monitored continuously throughout the supervised and unsupervised intervention. EORTC QLQ-C30: European Organisation for Research and Treatment of Cancer Quality of Life Questionnaire Core 30; EORTC QLQ-MY20: European Organisation for Research and Treatment of Cancer Quality of Life Questionnaire—Multiple Myeloma module; DXA: Dual energy X-ray absorptiometry; pQCT: Peripheral quantitative computed tomography; BMI: Body mass index; 30 STS: 30-s sit-to-stand test; YBT: Y-Balance Test; BPI: Brief Pain Inventory; FACT-BP: Functional Assessment of Cancer Therapy—Bone Pain; FACIT-F: Functional Assessment of Chronic Illness Therapy—Fatigue; OLBPDQ: Oswestry Low Back Pain Disability Questionnaire; PRO: Patient-reported outcomes; FACT-MM: Functional Assessment of Cancer Therapy—Multiple Myeloma; MyPOS: Myeloma Patient Outcome Scale; FES-I: Falls Efficacy Scale—International; PACES-8: Physical Activity Enjoyment Scale 8.

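### In the 12 randomised weeks adverse events are recorded on about 25 occasions in the exercise arm and once in the waitlist arm, so rates of non-serious events are not comparable between arms

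*Protocol article*

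**What the plan says.** Section 3.3.3 sets the collection rule: "The trial AEP will record at each testing and supervised training session whether an adverse event has occurred". For exercise done without supervision it adds: "Events at unsupervised sessions will require self-report by the participant to the trial AEP".

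The Abstract gives the exercise arm's schedule in the randomised period: "EX will complete 12-weeks of supervised (24 sessions) and unsupervised (12 sessions". For the waitlist arm it says: "The WT will be asked to maintain their current activity levels for the first 12-weeks". Table 1, footnote a, adds: "Baseline testing battery is repeated for waitlist control group after three months of usual care". Footnote c, attached to the adherence and safety rows, reads: "Adherence and safety will be monitored continuously throughout the supervised and unsupervised intervention".

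Two other provisions matter. Under the stepped-down supervision heading, "the AEP will telephone participants every two weeks to check on their adherence, any adverse events", but this belongs to the second three months of the programme. Section 3, on testing sessions in general, says: "Any alterations in medical status or medications, hospital admission, or concomitant study participation will be documented for future reference".

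**The concern.** The number of times a participant is asked about adverse events depends on the arm. Each supervised session is a recording occasion, and the waitlist arm has no sessions until its wait is over. The self-report route is written for unsupervised exercise sessions, and continuous monitoring is tied to the intervention. Neither is described as covering the wait.

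This matters because safety is one of the questions the trial says it will answer. Section 3.3.3 proposes to measure it through adverse event reporting, the Introduction says that the safety of resistance and impact training in myeloma still needs confirming, and the Conclusions list safety among the results. The Introduction also describes a high background of bone pain and lytic lesions from the disease itself, so a control rate would help the reader to interpret the exercise-arm events. Weeks 0–12 are the only period with a randomised group that is not exercising. If minor events are largely unrecorded in that group, a table of events by arm could make exercise look more harmful than it is, and no later analysis can recover events that nobody asked about.

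**Working it through.** **Plan's own figures.** The article states no adverse event rate or safety sample size, so there is none to reproduce. The session counts do reproduce: two supervised sessions a week for 12 weeks is 2 × 12 = 24, and one home session a week is 1 × 12 = 12, as in the Abstract.

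**Recording occasions per participant, weeks 0–12, after randomisation**

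| | Exercise | Waitlist |
|---|---|---|
| Supervised sessions | 24 | 0 |
| Test at 3 months | 1 | 1 |
| Total | 25 | 1 |
| Self-report route for home sessions | yes (12 sessions) | none described |

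At 75% attendance, the feasibility threshold in section 3.3.2, the exercise arm has 0.75 × 24 + 1 = 19 occasions. The imbalance is 25 to 1, or 19 to 1. The fortnightly calls are not counted because they begin after week 12 and so reach neither arm in this period.

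**What this could do to a rate comparison.** With the same true rate in both arms, the expected apparent rate ratio is the capture fraction with exercise divided by the capture fraction on the waitlist. The documents give no capture fractions. Assume 0.90 with exercise and 0.30 to 0.70 for one recall over 12 weeks:

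- 0.90 / 0.70 = 1.29
- 0.90 / 0.50 = 1.80
- 0.90 / 0.30 = 3.00
- 0.90 / 0.90 = 1.00 (equal capture)

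**Scale in this trial.** Sixty participants allocated 1:1 give 30 per arm. Assume one true event per person in 12 weeks in both arms. Expected recorded events are 30 × 1 × 0.90 = 27 with exercise, against 21, 15 or 9 on the waitlist. In a simulation with Poisson counts and a two-sided 5% comparison, the chance of a significant difference when none exists was:

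| Assumed true events per person | Waitlist capture 0.70 | 0.50 | 0.30 | Equal capture (0.90) |
|---|---|---|---|---|
| 0.5 | 10% | 26% | 58% | 5% |
| 1 | 14% | 46% | 87% | 5% |
| 2 | 23% | 75% | 99% | 5% |

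The event rates and capture fractions are assumptions, and the protocol plans no such test. The table shows how far a reader could be misled by comparing raw counts.

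**Is the single waitlist occasion secure?** Section 3.3.3 covers every testing session, which includes the end-of-wait test. Table 1 ticks safety at 3 and 6 months but not at baseline, and footnote a describes the end-of-wait test as a repeat of the baseline battery. Read from the table alone, that test carries no safety record. The two places need to agree.

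**The case against.** A reader might infer that the randomised period gives no usable control event rate at all. The documents do not support that. Section 3.3.3 includes testing sessions, so the waitlist arm has one record. Health history and disease status are in the battery it repeats, and section 3 has medical-status changes, medication changes and hospital admissions documented. The cost questionnaire also goes to both groups and covers hospital care and medication, although its timing during the wait is not explicit. Events that lead to admission therefore have a rough control rate.

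A reader might also infer that harm to bone or worsening pain cannot be told apart from the disease. For pain this fails: the Brief Pain Inventory, the bone pain subscale, the low back disability questionnaire and the quality-of-life symptom scales are given in the same way to both arms at baseline and 3 months.

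It is also fair to say that adverse events are a tertiary outcome, that no between-arm event comparison is stated, that the capture fractions are assumed, and that the case report form and full protocol are not shown and may hold a common set of questions. These points limit the size and certainty of the concern. They do not remove it. The unequal timing is stated in the article, and a report that lists events by arm invites the comparison whether or not a test is planned.

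**Conclusion.** The point holds in a limited form. As written, ascertainment in weeks 0–12 is about 25 occasions (19 at 75% attendance) against one, so event rates are not comparable between arms, particularly for non-serious events that leave no trace in an admissions or medication record. Over-counting in the exercise arm is the likely direction, though it is not demonstrated. The apparent rate ratio of about 1.3 to 3.0 under equal true rates rests wholly on assumed capture of 90% against 30–70%; the true size is unknown. The quality-of-life analysis is unaffected, as is the comparison of questionnaire-measured pain. The weakness lies in the safety statement that the trial intends to make, and it should be corrected because the remedy is cheap.

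**What to change.** 1. At the week-12 test, which both arms already attend, use one identical structured adverse event recall form covering the whole 12 weeks. Supplement it with the record of admissions and medical-status changes that section 3 already requires.
2. State that any between-arm safety statement will rest on that common record only.
3. Report events captured at training sessions separately, as a description of the exercise arm per session attended, and say that they have no waitlist counterpart.
4. Reconcile Table 1 with section 3.3.3 so that the end-of-wait test clearly includes a safety record.

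The cost is one short form at an existing visit and a few sentences of text. Two limits remain and should be stated in the report. A 12-week recall is coarser than a session log, and repeated asking at sessions may still prime recall in the exercise arm, so some imbalance will persist. Asking both arms at equal intervals during the wait would reduce this further, at the price of extra contacts with the waitlist arm.

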## 4. Data Collection, Management and Monitoring

All data from the study participants will be collected using a case report form designed for the standardization of data collection (available on request). Electronic copies of participant data, audio recordings, and transcripts of interviews will be stored in various modes (computer hard drive; external hard drive; and cloud-based systems), all of which will be de-identified and password protected, maintaining confidentiality at all times. Electronic data repositories will only be accessible by the study investigators and associated data analysts. All hard-copy files will be stored in a securely locked filing cabinet at the School of Human Movement and Nutrition Sciences, The University of Queensland. Disposal of hard-copy files will be performed in accordance with general procedures, the regulations of the administering ethical board and The University of Queensland.

Results will be made available to participants (including any publications that result from the project) upon individual request following the completion of the study. Individual participants will not be identified in any resultant manuscripts or reports of this trial.

The study investigators will permit study-related monitoring, audits, and inspections of all study related documents and facilities by the governing ethics committees. An independent data monitoring committee is not needed, given the role of the governing ethics committees.

## 5. Statistical Considerations and Data Analyses

A priori power calculations determined that a sample of 44 participants (*n* = 22 per group) will be needed to detect a mean difference of 6.7 points [51] between groups on the EORTC QLQ-C30 MY20 after the 3-month supervised exercise phase, with 80% power and 5% alpha. To account for an anticipated dropout rate of 25%, 60 participants will be recruited to the study. A difference of 6.7 on the physical function subscale of the EORTC QLQ-C30 MY20 questionnaire, determined by receiver operating characteristic curve analysis, corresponds to the minimum clinically meaningful change considered important by people with MM [51].

Data will be analyzed using the Stata statistical software package (version 15.0, StataCorp, College Station, TX, USA). Data entry will be performed in duplicate, and accuracy will be assessed with automatic cross-checking procedures. Range checks for data values will be performed to promote data quality. Data will be assessed for normality using the Shapiro–Wilk test. Subsequent analyses will include standard descriptive statistics, *t* tests, correlation, regression, and one-way repeated measures ANOVA or the comparable non-parametric test as necessary to examine differences among timepoints. Each model will include covariates, as appropriate, and will be adjusted using the baseline value as a fixed continuous covariate. For accelerometer data, means and 95% confidence intervals will be calculated and repeated measures accounted for across multiple days within participants. Quality of life questionnaire items will be analyzed using random effects mixed modelling with Fisher’s least significant difference tests for post hoc analyses to compare mean changes in outcomes between groups at each assessment period, with time and group as the fixed factors. A time × group interaction term will be used to formally test for differences between groups (alpha = 0.05).

The number of participants who provide data at each timepoint will be reported, with reasons as to why participants did not attend. Incomplete data and missing values will primarily be managed using intention-to-treat analyses, using a 70% cut-point for adherence. To ensure the robustness of the findings, a secondary sensitivity analysis will be performed [109]. Non-continuous data will be analyzed using multinomial logistic regression. Metabolomics and lipidomics data will be evaluated using multivariate statistics, including principal component analysis and sparse partial least squares discriminant analysis. The blood molecular time-series measures will be analyzed to determine the metabolic and immune pathways altered by exercise and to determine biomarkers of responders for physical fitness, fatigue, and pain, if any. Exercise and control groups will be further stratified by therapy and remission duration. All tests will be two-tailed, and an alpha level of 0.05 will be applied as the criterion for statistical significance. There are no interim analyses planned or early trial termination guidelines.

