### 3.1. Primary Outcome

#### Cancer-Specific Quality of Life (EORTC QLQ-C30 and QLQ-MY20)

The primary outcome of this study is HRQoL after the 3-month supervised exercise intervention compared with the waitlist control. HRQoL will be measured using the overall HRQoL summary score for the core HRQoL questionnaire of the European Organisation for Research and Treatment of Cancer Quality of Life Questionnaire (EORTC QLQ-C30, version 3.0) [46]. The EORTC QLQ-C30 is a widely used and well-validated cancer-specific instrument [3] with good psychometric properties in solid tumors [47,48]. It has acceptable reliability and validity in MM (Cronbach’s α = 0.70–0.92, except role function = 0.54), with an excellent ability to discriminate between patients in different objective disease states and a high responsiveness to changes in patients’ clinical status over time [3,49]. In a recent Delphi analysis, consensus was reached to collect patient-reported outcomes using the EORTC QLQ-C30 in patients with MM [50]. The minimal important difference (MID), defined as the smallest change in a HRQoL score considered important to patients that would lead the patient or clinician to consider a change in therapy, will be based on those estimated for individual scales of the QLQ-C30 in patients with MM [51].

The EORTC QLQ-C30 summary score encompasses all symptom (e.g., fatigue, pain) and function domains (e.g., emotional and social functioning) assessed by the QLQ-C30. The summary score is a strong prognostic factor for overall survival above and beyond that provided by clinical and sociodemographic variables for patients with MM [7]. The summary score also appears to have more prognostic value than the global QoL, physical functioning, or any other scale within the QLQ-C30 [7].

The European Organisation for Research and Treatment of Cancer Quality of Life Questionnaire Multiple Myeloma module (EORTC QLQ-MY20) is a reliable and valid instrument, recommended as a supplement to the QLQ-C30 instrument in patients with MM (Cronbach’s α = 0.70–0.92) [52]. As with the QLQ-C30, QLQ-MY20 domain scores are averaged and transformed linearly to a score ranging from 0–100. A high score for disease symptoms and side effects of treatment represents a high level of symptomatology or problems, whereas a high score for future perspective and body image represents better outcomes.

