**Figure 2 curroncol-29-00077-f002:**
[figure not shown]
Schematic representation of the 12-week supervised exercise intervention protocol. HR_peak_: peak heart rate; OMNI-RES: OMNI-Resistance Exercise Scale of Perceived Exertion; reps: repetitions; mins: minutes.

**Table 1 curroncol-29-00077-t001:** Schedule of data collection.

	Timepoint			
Assessment or Outcome	Baseline ^a^	3-Months	6-Months	12-Months
*Screening*				
Participant eligibility	✓			
Informed consent	✓			
Doctor’s consent	✓			
Health history and disease status	✓	✓	✓	✓
Demographics	✓			
Concomitant research study participation	✓	✓	✓	✓
*Primary Outcomes*				
Quality of life (EORTC QLQ-C30 and QLQ-MY20)	✓	✓	✓	✓
*Secondary Outcomes*				
Cardiorespiratory fitness (V̇O2peak)	✓	✓	✓	✓
Body composition and bone mineral density (DXA)	✓	✓	✓	✓
Bone architecture (pQCT)	✓	✓	✓	✓
Anthropometry (BMI, waist, and hip circumferences)	✓	✓	✓	✓
Strength (30STS, grip strength, mid-thigh pull)	✓	✓	✓	✓
Balance (Single leg stance, YBT)	✓	✓	✓	✓
Pain and bone pain (BPI, FACT-BP)	✓	✓	✓	✓
Fatigue (FACIT-F)	✓	✓	✓	✓
Functional disability (OLBPDQ)	✓	✓	✓	✓
Myeloma-specific PROs (FACT-MM, MyPOS)	✓	✓	✓	✓
Falls self-efficacy (FES-I)	✓	✓	✓	✓
Blood collection for blood biomarkers, metabolomics, and lipidomics	✓	✓	✓	✓
Self-reported physical activity (Godin)	✓	✓	✓	✓
Sedentary behavior and physical activity (ActiGraph™ accelerometry)	✓	✓	✓	✓
Exercise enjoyment (PACES-8) ^b^		✓		
*Tertiary Outcomes*				
Qualitative analysis (Semi-structured interviews)			✓	
Adherence ^c^		✓	✓	
Safety (Adverse and serious adverse events) ^c^		✓	✓	

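### The 80% power is not shown for the primary endpoint: the 6.7-point target is justified only for physical function, while the primary outcome is the QLQ-C30 summary score

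*Protocol article*

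**What the plan says.** **Primary outcome (protocol article, section 3.1).** The time and contrast are fixed: "The primary outcome of this study is HRQoL after the 3-month supervised exercise intervention compared with the waitlist control". So is the score: "HRQoL will be measured using the overall HRQoL summary score for the core HRQoL questionnaire", that is, the QLQ-C30. The section explains that "The EORTC QLQ-C30 summary score encompasses all symptom (e.g., fatigue, pain) and function domains". It presents the QLQ-MY20 as a separate supplementary module with its own domains.

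**Importance threshold (section 3.1).** The minimal important differences "will be based on those estimated for individual scales of the QLQ-C30 in patients with MM [51]". None is given for the summary score.

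**Sample size (section 5).** 44 participants, 22 per group, are needed "to detect a mean difference of 6.7 points [51] between groups on the EORTC QLQ-C30 MY20" after the supervised phase, with 80% power and 5% alpha. Allowing for 25% dropout, 60 are recruited. The paragraph then explains where the target comes from: "A difference of 6.7 on the physical function subscale of the EORTC QLQ-C30 MY20 questionnaire" is said to be the smallest change that people with myeloma regard as important. Both mentions of 6.7 cite the same reference, the one section 3.1 cites for individual-scale thresholds.

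**Schedule (Table 1).** Under the primary outcomes the row reads "Quality of life (EORTC QLQ-C30 and QLQ-MY20)". The heading within section 3.1 also names both questionnaires.

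**The concern.** A power statement supports the primary analysis only if its target difference and variability refer to the score being analysed. Here the score analysed is a composite of all QLQ-C30 symptom and function domains, and the target is explained only by one of those domains. What counts as an important difference on one subscale need not be important on the composite, and the two scores need not vary by the same amount. The questionnaire label in the power sentence does not settle which score was meant, because the QLQ-C30 and QLQ-MY20 are separate instruments and section 3.1 defines no joint score.

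Two things are at stake. The 80% cannot be read as the chance of detecting an important effect on the primary endpoint. And when the result arrives, its confidence interval will have no prespecified summary-score threshold to be compared with, whichever way the result goes.

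**Working it through.** **Inputs from the protocol article.** Target difference 6.7 points; 22 per group; 80% power; 5% alpha; 25% dropout; 60 recruited (all section 5). Two-tailed tests (section 5). 1:1 allocation (section 2.4). Adjustment for the baseline value (section 5). No SD and no baseline-to-follow-up correlation is given for any scale.

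**Step 1. The plan's own figures.**
- Dropout: 44 / (1 − 0.25) = 58.7, so 59. By arm, 22 / 0.75 = 29.3, so 30 per arm and 60 in total. The recruited number reproduces.
- The 44 cannot be reproduced forwards without an SD, so it is solved backwards.

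**Step 2. The SD implied by 22 per group.**
- Normal approximation: d = √(2/22) × (1.960 + 0.842) = 0.845, so SD = 6.7 / 0.845 = 7.93.
- Two-sample t test (noncentral t): d = 0.865, so SD = 6.7 / 0.865 = 7.75.

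The stated 80% therefore holds for 6.7 points if the relevant SD (raw, of change, or baseline-adjusted) is about 7.75. If baseline adjustment was assumed, the raw SD would be 7.75 / √(1 − r²): 8.9 at r = 0.5 or 10.9 at r = 0.7.

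**Step 3. Sensitivity, for illustration only.** The SDs and correlations below are assumptions, taken on both sides of 7.75. Power is for 6.7 points with 22 per arm, t test, two-sided 5%. Baseline adjustment replaces SD by SD × √(1 − r²); at r = 0.7 the factor is 0.714. The detectable difference is 0.865 × SD.

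| Assumed raw SD | Power, unadjusted | Power, adjusted, r = 0.7 | Detectable difference at 80%, unadjusted |
|---|---|---|---|
| 6 | 95% | above 95% | 5.2 |
| 7 | 87% | above 95% | 6.1 |
| 7.75 | 80% | above 95% | 6.7 |
| 10 | 58% | 86% | 8.6 |
| 12 | 44% | 72% | 10.4 |
| 15 | 30% | 53% | 13.0 |

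**Step 4. The target matters as much as the SD.** Keep the SD at 7.75 and suppose the important difference on the summary score were not 6.7. Power would be 39% for 4 points, 55% for 5 points and 92% for 8 points. These targets are assumptions too; the article gives none for this score.

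**The case against.** Section 3.1 is explicit about the primary endpoint, and the power sentence itself names the questionnaire rather than physical function. The physical-function sentence may be only the rationale for choosing 6.7, and the SD behind the calculation could have come from the summary score. A composite may also vary less than a single subscale, and baseline adjustment adds precision.

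Much of this stands, and it rules out several stronger readings.

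- *The trial is underpowered.* A reader might infer this from the power figures at SD 10 and above. The documents do not support it: no SD is given, SDs below 7.75 give more than 80%, and SD 10 with a correlation of 0.7 gives 86%.
- *There are three rival primary endpoints, open to choice after the fact.* A reader might infer this from section 3.1, section 5 and Table 1 together. Section 3.1 fixes one score, one time and one contrast. Table 1 is a data-collection schedule listing instruments, and the section 5 paragraph is a power statement. The labels are loose, but neither defines a competing endpoint.
- *The missing SD is a defect in itself.* A condensed article may leave it to the full protocol.
- *An important change was misused as a difference between group means.* This is common practice and adds nothing to the mismatch.
- *A null result could not exclude an important effect.* That depends on the confidence interval set against a threshold, not on prior power. The gap is the absent threshold.

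What the objection does not remove is the stated mismatch: the only justification in the text for 6.7 belongs to one component of the primary score.

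**Conclusion.** The point holds in a limited form. The 80% power is undemonstrated for the QLQ-C30 summary score; it is not shown to be too low. This rests on the article's own wording in sections 3.1 and 5, not on an omission. What 22 completers per arm deliver at 80% power is a standardised difference of 0.865, by an unadjusted two-sided t test. That equals 6.7 points only if the relevant SD is about 7.75. Every other power figure above depends on an assumed SD, correlation or target. Because this is the trial's primary comparison and the correction is cheap, it should be made.

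**What to change.** Keep n = 60 and amend the text.

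1. In section 5, name the QLQ-C30 summary score at 3 months in place of the combined questionnaire label.
2. State and justify a target difference for that score, or justify carrying 6.7 over to it. Use the same value as the importance threshold when the primary result is interpreted.
3. State the SD, and the correlation if baseline adjustment is assumed. Blinded pooled baseline summary scores, which the schedule already collects, could supply the SD.
4. Restate the power or the detectable difference: 22 completers per arm detect 0.86 SD at 80% power, which with the stated SD converts to points.
5. Use 6.7 only to interpret the physical function scale, unless step 2 justifies it for the summary score.
6. Align the section 3.1 heading and Table 1 so that the summary score alone is primary, with QLQ-MY20 and the individual scales secondary.

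The cost is a wording amendment and one recalculation, with no extra participants. The drawback is that the stated detectable difference may look less favourable than 6.7 points.
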